### Data acquisition and biological parameter assessment

The recruited patients in this study will receive a participant ID, which will be labelled in the chart containing the personal information of the participants. Only investigators involved in this study will have the right to access the participant IDs on an as-needed basis.

The following data will be collected from all participants:Clinical, laboratory, and imaging-study findings on day 0, day 3, day 7, day 14, and day 28 (if available)Emergency medical service (EMS) record, ICU mortality, ICU length of stay, hospital mortality, hospital length of stay, 28-day all-cause mortality, and inpatient costDetails on the decision-making process

If patients are discharged early, investigators will call them back to the hospital as outpatients for free data acquisition and examinations.

The clinical parameters will include age, sex, cause of SCA, comorbidities, APACHE II scores, and SOFA scores. The EMS record contains the time of the call for EMS, the time of arrival, the initial cardiac rhythm, and management information. The data above will be collected on the day of enrolment and 28 days after registration. The schedule of the trial is shown in Fig. 2.

**Fig. 2 Fig2:**
[figure not shown]
Standard Protocol Items: Recommendations for Interventional Trials (SPIRIT) timeline of measurements. Laboratory examinations include tests for inflammation parameters (C-reactive protein and procalcitonin), complete blood counts, general urine analyses, liver function tests (ALT, AST, ALP, TBIL, and GGT), renal function tests (BUN, Scr), and tests to measure troponin and lactic acid

Routine laboratory examinations (complete blood counts (CBCs), C-reactive protein (CRP) and procalcitonin (PCT) tests, liver function tests (ALT, AST, ALP, TBIL, and GGT), and renal function tests (BUN and Scr)) will be performed by the clinical laboratory of Guangdong Provincial Hospital of Chinese Medicine.

Investigators will be trained to collect trial data according to the standard protocol. Data will ultimately be input into the Clinical Trial Management Public Platform, ResMan, designed for clinical trials. Double data entry will be performed by two researchers independently and will be checked by the third data clerk separately. All collected forms will be kept in the scientific research department of Guangdong Provincial Hospital of Chinese Medicine. Investigators will be trained to collect trial data according to the standard protocol.

Any adverse event that occurs in participants, regardless of whether it is related to the EA, will be recorded from recruitment to the 28th day. Severe adverse events and unexpected adverse events will be reported to the Ethics Committee within 2 days. EA will be suspended, and symptomatic treatment will be offered when needed. The principal investigator will decide whether the participants should discontinue the trial.

Both data and safety will be monitored by the Institutional Review Board and the scientific research department of Guangdong Provincial Hospital of Chinese Medicine, independent of the sponsor, with no competing interests.

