## Background

Sudden cardiac arrest (SCA) is a significant cause of death worldwide, and more than 550,000 deaths due to SCA occur annually in the USA and Europe [1]. A recent study showed that epinephrine, the first-line medication for patients with SCA, was associated with more severe neurological impairment in survivors than placebo in adults with out-of-hospital cardiac arrest (OHCA) [2]. In addition, SCA patients will have sepsis-like changes, which may be caused by ischaemia, hypoxia, and reperfusion injury, after the return of spontaneous circulation (ROSC), resulting in multiple organ dysfunction syndromes (MODSs) and a poor prognosis,. This series of reactions is called postcardiac arrest syndrome (PCAS) [3]. According to studies performed in the USA, Europe, and Asia, whether in adults, children, or infants, the mortality rate of PCAS patients is 65–80% [4–8]. The high mortality rate can be attributed to a unique pathophysiological process. The special features of this unique pathophysiological process of PCAS are often superimposed on the disease or injury that caused the cardiac arrest and underlying comorbidities [3]. There are four critical components of PCAS: brain injury [9, 10], myocardial dysfunction [11, 12], systemic ischaemia/reperfusion response [13], and persistent precipitating pathology [14]. Therefore, therapies focusing on a single organ may further damage other damaged organ systems. Targeted temperature management (TTM) is currently the only clinically proven method to improve SCA patients’ survival and neurological outcomes after the ROSC [15, 16]; however, TTM is still associated with a series of problems that have not been completely resolved [17].

Acupuncture is a crucial therapy in traditional Chinese medicine (TCM). Acupuncture involves the insertion of fine needles at “acupoints”, followed by stimulation via manual or mechanical techniques [18]. It has been reported that acupuncture may have a bidirectional regulating effect and an anti-systemic inflammatory response effect [19, 20]. The acupuncture effect of balancing the autonomic nervous system has been demonstrated to inhibit neuronal apoptosis and reduce oxidative stress [21–23]. These effects are in line with the critical components of PCAS mentioned above.

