### EA treatment

Disposable stainless steel acupuncture needles will be inserted at the Baihui acupoint (GV20, located at the intersection of the sagittal midline and the line linking the ears) and unilaterally on the side of the left leg at the Zusanli acupoint (ST36, situated on the front to one side of the leg, 3 *cun* below the acupoint ST35 and a cross-finger (middle finger) away from the leading edge of the tibia) to a depth of approximately 0.5 cm [28]. Furthermore, an EA instrument (Suzhou Medical Supplies Factory Co., Ltd., Jiangsu, China) will be connected to perform EA stimulation for 30 min using a dense-dispersed wave at frequencies of 20 and 100 Hz. The current intensity will be less than 10 mA (adjusted to induce a slight muscle twitch), and the pulse width will be 0.5 ms. One of the two electrodes of the EA stimulator will be connected to the needle at GV20, and the other electrode will be connected to the needle at ST36. This EA intervention will begin immediately after the ROSC for 20 min and will continue for up to 14 days, discharge, or death, whichever comes first. The EA will be performed by [name], [name], or [name], who will conduct the research and have previously received equal training.

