### Outcome measures

The primary feasibility outcomes are as follows:Evaluate the acceptability and compliance of EA in PCAS as an additional intervention of usual care.Explore the feasibility of recruiting, randomizing, and retaining participants.Evaluate outcome measures’ appropriateness.Collect data for effect size calculation in future sample size calculating.Develop an appropriate protocol for further study.

The length of time for recruitment of 50 eligible patients, recruitment rate and dropout rate will be measured. Successful recruitment is defined as at least half (50%) of eligible patients enrolled, with a dropout rate of no more than 20%.

The secondary patient-centred outcomes include the following:We define a favourable neurological outcome as a cerebral performance category (CPC) score of 1 or 2 on the 28th day after the ROSC. We define an ROSC as a spontaneous pulse and blood pressure, an abrupt sustained increase in end-tidal CO_2_ partial pressure (PETCO_2_) (typically ≥ 40 mmHg), or spontaneous arterial pressure waves with intra-arterial monitoring.Neurological scores: Glasgow Coma Scale (GCS) score, CPC score, modified Rankin Scale (mRS) score, and cranial computed tomography (CT) findings;Evaluation of cardiac function: troponin and lactic acid levels and echocardiography parameters.Sequential Organ Failure Assessment (SOFA) scoresAcute Physiology and Chronic Health Evaluation (APACHE) II scoresLength of stay in the ICU, length of hospital stay, hospital mortality/discharge, and hospital costsAdverse events

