### Statistical analysis

The data will be analysed statistically according to the method of a previous study [32]. Enrolled participants who cannot continue the study or follow up after treatment will remain in an “intention to treat” analysis. All statistical analyses will be performed with SPSS (version 17.0, Chicago, USA) for Windows by researchers not implementing the intervention. The analysis of this trial will be mainly descriptive focusing on estimation rather than hypothesis testing. All baseline outcomes will be summarized for each group using the appropriate descriptive statistics. No formal comparison of groups will take place. A full statistical analysis plan will be developed prior to the final analysis of the trial.

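### After an adverse event the principal investigator decides on exit from the trial, and nothing secures the day-28 neurological outcome of patients who stop electroacupuncture or leave

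*Protocol article*

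**What the plan says.** The adverse-event rules stand at the end of the section Data acquisition and biological parameter assessment, after Fig. 2.

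- **Recording:** "Any adverse event that occurs in participants, regardless of whether it is related to the EA, will be recorded from recruitment to the 28th day".
- **Treatment:** after the sentence on reporting severe and unexpected events, "EA will be suspended, and symptomatic treatment will be offered when needed".
- **Participation:** "The principal investigator will decide whether the participants should discontinue the trial".

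Other parts of the article bear on what happens next:

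- **Outcome measures** defines a favourable outcome as a "cerebral performance category (CPC) score of 1 or 2 on the 28th day after the ROSC". It also sets a dropout rate of at most 20% as part of successful recruitment, and lists acceptability and compliance of EA among the feasibility outcomes.
- **Data acquisition** lists, for all participants, "Clinical, laboratory, and imaging-study findings on day 0, day 3, day 7, day 14, and day 28 (if available"), and separately 28-day all-cause mortality. Recall to the hospital is promised only for patients discharged early.
- **Statistical analysis:** "Enrolled participants who cannot continue the study or follow up after treatment will remain in an “intention to treat” analysis".
- **Randomization** says that the number of a patient who withdraws is invalidated, and that the first 52–60 patients will be taken.
- **Blinding and masking** names outcome assessors, laboratory technicians and biostatisticians as blinded. The principal investigator is not named.

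**The concern.** Stopping a treatment and leaving a trial are different events. The adverse-event rules deal with the treatment in one sentence and then, in the next, give the investigator a decision on participation in the trial. The article never describes the usual middle course, in which the treatment stops and observation continues.

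Three features make the resulting loss hard to ignore. It follows an adverse event, so it is likely to be related to prognosis. The decision has no stated criteria and is made by someone not listed as blinded. The suspension step leading up to it exists only in the EA arm, so the route to exit may be used unequally even though the decision itself covers both arms.

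Three outputs of the pilot are at stake: the day-28 CPC and mRS data meant to inform the main trial's effect size, the dropout criterion, and the measure of EA compliance. If stopping EA and leaving the trial are recorded as one event, the last two cannot be told apart.

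**Working it through.** **1. The plan's own figure.** Inputs: 20 participants or more, 20% expected dropout and 50 to be recruited (Sample size determination); 1:1 allocation (Randomization). The article does not say whether the 20 is per arm; I read it so.

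- N per arm = 20 / (1 − 0.20) = 25, and 2 × 25 = 50. The stated 50 reproduces.
- Losses allowed by the 20% criterion: 0.20 × 50 = 10.

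**2. Does any section secure day-28 CPC after exit?**

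| Section | What it secures | What it leaves open |
|---|---|---|
| Statistical analysis | Membership of the analysis set | Where the outcome value comes from |
| Data acquisition, visit schedule | Planned visits for all participants | Day-28 findings depend on availability |
| Data acquisition, recall | Return visits after early discharge | Patients discontinued by the investigator |
| Data acquisition, mortality | 28-day vital status | CPC and mRS in survivors |
| Adverse-event rules | Event recording to day 28 | Whether recording continues after exit |
| Randomization | Nothing; the number is invalidated on withdrawal | Whether this also covers investigator-led exit, and how it fits with intention to treat |

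None secures the neurological outcome of a discontinued survivor.

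**3. Size, by illustration.** Assumptions not in the document: n = 25 EA patients, x known favourable outcomes, m missing. All n stay in the denominator, as the intention-to-treat sentence requires.

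- Lower bound = x / n (all missing unfavourable); upper bound = (x + m) / n (all missing favourable).
- x = 5, m = 1: 5/25 = 20% to 6/25 = 24%.
- x = 5, m = 3: 20% to 8/25 = 32%.
- x = 5, m = 5: 20% to 10/25 = 40%.
- x = 3, m = 5: 3/25 = 12% to 8/25 = 32%.
- x = 7, m = 5: 7/25 = 28% to 12/25 = 48%.

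**4. How far mortality data narrow this.** A patient known to have died is unfavourable, so only survivors can raise the upper bound. The Background states that "the mortality rate of PCAS patients is 65–80" per cent, without a time point. If that applied at day 28, expected survivors among 25 would be 25 × 0.20 = 5 to 25 × 0.35 = 8.75. With five favourable survivors already known, about 0 to 4 of the missing could be survivors. The upper bound would then be between 5/25 = 20% and 9/25 = 36%. The 20–40% range is therefore the outer limit, with nothing known about the missing five.

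**5. Compliance against dropout.** Suppose five EA patients stop EA. If they stay under observation, dropout from this cause is 0/50 = 0%. If stopping is counted as leaving, it is 5/50 = 10%, half of the 20% allowance. The same clinical course gives either figure, depending on a distinction that the article does not make.

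**The case against.** The strongest reply is that the article shows an intent to follow everyone. Data are listed for all participants, 28-day mortality is among them, and adverse events are recorded to day 28. It never says that observation ends when a patient discontinues. The trial is a descriptive pilot without formal comparison, and five losses would still be within the dropout limit. Much of this stands: it limits the harm and confines the main risk to survivors. It does not supply a CPC for a patient who has left, and an analysis plan written later cannot recover an assessment that was never made.

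A reader might infer more than the text supports:

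- **That only EA patients face removal.** The sentence speaks of participants and so covers both arms. Imbalance is an inference from the EA-only suspension step and from open treatment.
- **That most EA patients would have EA suspended, given the quoted mortality.** The qualifier at the end of the suspension sentence may govern suspension as well as symptomatic treatment, and no section gives a rate of events that trigger suspension.
- **That the section EA treatment contradicts the suspension rule.** It says that EA "will continue for up to 14 days, discharge, or death, whichever comes first". That sets a maximum course, and a safety interruption within a maximum is no contradiction.
- **That the favourable rate would be inflated to 5/20 = 25%, or to 5/15 = 33% with ten exits.** Those figures drop patients from the denominator, whereas the intention-to-treat sentence keeps them at 25.

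**Conclusion.** The concern holds as a weakness in a stated conduct rule. After an adverse event the article provides for a decision on leaving the trial, gives no criteria for it, and nowhere secures day-28 CPC or mRS for those who leave. Informative loss is plausible. Loss that differs between the arms is possible but not shown.

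In the illustration, five missing outcomes among 25 EA patients leave the favourable rate anywhere from 20% to 40%, and less wide if deaths are captured. This rests on assumed counts and on 25 patients per arm; the article gives no expected number of discontinuations. The effect on the feasibility results needs no such assumption: without separate definitions, compliance and dropout overlap.

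The descriptive pilot design limits the consequences. Even so, the Trial status section says that recruitment is under way, so outcomes not collected now may be lost to the main trial's planning.

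**What to change.** 1. State in the adverse-event rules that suspending or stopping EA, or an investigator's decision after an adverse event, does not end data collection. Every randomised patient in either arm is followed to day 28 for CPC, mRS, mortality and adverse events, unless consent for follow-up is withdrawn.
2. Record the end of EA and the end of study participation as separate items. Report the first under compliance and the second as dropout against the 20% criterion, by arm.
3. Reconcile Randomization, the adverse-event rules and Statistical analysis on patients who discontinue: whether their number is invalidated, whether they are replaced, and how that fits with the intention-to-treat statement.

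When and why EA is suspended, and what follows a suspension, is for the sponsor to clarify; no clinical rule is proposed here.

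The cost is protocol wording, one case-report-form field and a few more day-28 assessments.

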### Statistical analysis

The data will be analysed statistically according to the method of a previous study [32]. Enrolled participants who cannot continue the study or follow up after treatment will remain in an “intention to treat” analysis. All statistical analyses will be performed with SPSS (version 17.0, Chicago, USA) for Windows by researchers not implementing the intervention. The analysis of this trial will be mainly descriptive focusing on estimation rather than hypothesis testing. All baseline outcomes will be summarized for each group using the appropriate descriptive statistics. No formal comparison of groups will take place. A full statistical analysis plan will be developed prior to the final analysis of the trial.

## Discussion

In addition to high mortality, SCA remains a cause of disability in survivors [17]. Hypothermia has been applied for the treatment of SCA from the 1950s to the present. Hypothermia has been shown to improve neurological outcomes and survival in patients with severe ischaemia–reperfusion brain injury after the ROSC [6, 33–35]. Animal studies have shown that the mechanism underlying the effect of mild hypothermia on PCAS is complicated and that it does not merely involve a decline in brain metabolism [36, 37]. Furthermore, TTM is currently the only clinically proven way to improve neurological outcomes and survival after the ROSC. However, TTM is still associated with a series of problems that have not been completely resolved.

Retrospective studies have shown that for IHCA, the earlier TTM is implemented, the higher the proportion of favourable neurological outcomes, and this trend is also seen in the survival rate [38, 39]. Because of the low quality of evidence, the data showing that the effects of prehospital induction of cooling are superior to those of in-hospital initiation of cooling are not convincing. Moreover, prehospital cooling might result in higher rearrest rates after the ROSC [40, 41]. The delay of mild hypothermia in retrospective studies may be related to problems such as a lack of simplified procedures and experience in PCAS, hemodynamic instability, recurrence, and coronary angiography. Therefore, whether early initiation of mild hypothermia can result in a favourable neurological outcome and induce hypothermia remains controversial.

Acupuncture is an integral part of TCM. Many documents show that it was the primary means of treating emergencies such as SCA in ancient times. Whether acupuncture can be used as a new technique in CPR to improve survival with a favourable outcome is worthy of in-depth study.

Studies have shown that after EA, oligodendrocyte regeneration increases [42, 43], motor and memory function improves [44, 45], and cognitive impairment is ameliorated [46]. The role of EA is related to the upregulated expression of neurotrophin-4/5-tyrosine receptor kinase B (NT4/5-TrkB) signalling [42], cAMP response element-binding protein/brain-derived neurotrophic factor (CREB/BDNF) signalling [44, 45, 47, 48], stromal cell-derived factor-1α (SDF-1α) [49], B cell lymphoma-2 (Bcl-2) and B cell lymphoma-2 related X protein (Bax) [46, 50]. Animal studies have shown that acupuncture at GV20 and ST36 can significantly reduce blood–brain barrier permeability and brain oedema, and the effect of acupuncture may inhibit the expression of phosphorylated caveolin-1 in endothelial cells [51]; downregulate reactive oxygen species (ROS) and NADPH oxidase type 4 (NOX4) [52]; and upregulate matrix metalloproteinase-2 (MMP2), aquaporin-4 (AQP4) and aquaporin-9 (AQP9) [53]. It was found in a middle cerebral artery occlusion (MCAO) rat model study that EA could inhibit neuronal apoptosis, impede the activation of microglia and inhibit inflammatory responses [54]. Acupuncture may involve specific effects on the protease A (PKA)/CREB pathway [23] and erythropoietin (EPO)-mediated Janus family tyrosine kinase 2 (JAK2) signal transduction and transcription activator 3 (STAT3) cell pathway [22], reduce S100B-mediated neurotoxicity [55] and finally achieve anti-apoptosis. In addition, anti-ischaemic apoptosis may be obtained through the downregulation of the oxidative stress response, which is associated with a decrease in tumour necrosis factor α (TNF-α), interleukin 6 (IL-6), neuron-specific enolase (NSE), malondialdehyde (MDA), superoxide dismutase (SOD), and catalase (CAT) in the serum and hippocampus [56]. Furthermore, EA reduced the infarct area and increased the ejection fraction (EF) by inhibiting the expression of NLR family pyrin domain containing 3 (NLRP3) and AMP-activated protein kinase (AMPK)-dependent autophagy in an animal study of an acute myocardial infarction rat model [57, 58].

Our decision to use an EA in PCAS is based on the results of our retrospective study published in Chinese, in which we found that EA attenuates the multiorgan failure of patients with PCAS [59], and those of a systematic review indicating that acupuncture ameliorates the injuries induced by experimental sepsis [60]. Whether EA is associated with mortality or a favourable neurological outcome after PACS is unclear. However, this trial is the first registered interventional and experimental study evaluating the potential benefits of EA on the neurological outcome of PCAS. The results of this trial might establish the importance of EA as a promising complementary strategy for the treatment of PCAS.

This study is the first study of EA for the treatment of SCA. The initial design was to consider SCA due to all causes; however, the ethics committee suggested that a pilot study in a focused area was needed to clarify the feasibility and safety of EA. The next step will be to expand the research. Therefore, there are several limitations to this trial. First, this is a pilot study with a small sample size and no blinding of the recruited participants. Second, the causes of SCA vary, and EA may be useful only for some causes of SCA, which could ultimately lead to bias; therefore, matched control and subgroup analyses are needed. Third, the treatment strategy received by ICU patients is highly complicated; therefore, the results of this trial might not be adequately explained solely by the therapeutic effect of EA. Fourth, as stated throughout this paper, this was a pilot study and no sample size calculation was performed; this was not powered for hypothesis testing of clinical outcomes. The clinical results will be treated as preliminary and interpreted with caution.

